### Process evaluation

The intervention will be accompanied by a full and detailed process evaluation to include assessment of the context, fidelity, implementation and reach of the intervention, and barriers to implementation [44, 45]. It will include an assessment of contamination of control schools where science teachers have moved from intervention schools. Oversight of the process evaluation will be led by a health psychologist (MB) who has extensive experience in the field of process evaluation and was involved in the recent MRC publication of guidelines for process evaluation [46]. She is independent from the implementation of the intervention and so can provide an unbiased oversight. An education researcher (AC) will be responsible for conducting observations in schools to ensure fidelity to the teaching programme and whilst she is involved in the professional development for the school teachers, in order to establish a credible relationship with the education community, she is independent of the implementation of the intervention from that point onwards.

### Statistical analyses

We will perform an intention-to-treat analysis using multi-level models for the quantitative data. Specifically, random effects models will be used to take account of the clustered nature of our data. Multi-level logistic (for rare outcomes) or Poisson regression models with robust variance (for more common outcomes) will be used for binary outcome variables and multi-level linear regression for continuous measures. The number of clusters is relatively small, and summary analyses will be conducted at school level, not least as this will allow us to feedback school-level data to the schools that have been involved in the trial. Our endpoint will be the results of a 12-month follow-up with adjustment for baseline responses included in the modelling.

Planned subgroup analyses would focus on whether there are different effects for boys and girls. We will analyse the uptake of LifeLab in different ethnic groups and in those who are more disadvantaged. Compliance will also be assessed in relation to various confounding factors to assess the bias associated with the different consent procedures imposed on us by the schools for the intervention and control groups. Sensitivity analyses will be conducted as appropriate using sampling from the intervention arm to try to account for this bias. In practice, during our pilot work, as schools do not want children remaining in school when the rest of the class is out on a trip, very few children are not included in the intervention arm, and thus we are confident that there is likely to be little difference in response rates between the two arms of the trial.

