## Methods/Design

### Trial design

The target population for the evaluation is the state secondary schools in Southampton and surrounding areas. We propose to evaluate LifeLab through a cluster randomised control trial, recruiting Year 9 students (aged 13 to 14 years) from 32 state secondary schools/academies (approximately 2,500 students) to take part in the project. Each school will be randomly allocated to either ‘control’ or ‘intervention’ status. During year 1 (school year 2014–15) we aim to recruit 16 schools; eight will therefore be intervention schools and their Year 9 students will take part in the LifeLab programme, whereas the other eight schools will form the control group. During year 2 (school year 2015–2016), this process will be repeated. Schools that are randomised to the control arm of this intervention will be invited to attend LifeLab in the academic year *following* the year they contribute to the control group. Questionnaires will be administered to control and intervention students after recruitment (baseline questionnaires) and again approximately 12 months after the baseline questionnaires were completed. There may be some small loss to follow-up due to children moving schools during the school year, but we do not anticipate this having major impact; in our current small-scale trial, at the 12-month follow-up, 2 % of the students were unavailable to participate due to moving schools. We emphasise in our discussions with schools during the recruitment phase the need to track the students over the length of the trial and ask that schools provide us with the new school details for those students who have left. We will then contact the new schools to request permission to work with those students who have moved. Good working relationships with the schools have been developed over many years and should assist in minimising any dropout at the school level. The Heads of Science of all the Southampton and many Hampshire secondary schools are enthused by LifeLab and are committed to it. They have been involved from a very early stage and have always been keen for their students to take part in our taster and pilot activities. We envisage good take-up within the schools and do not foresee recruitment difficulties. We appreciate that the control schools may wish to receive the intervention straight away, but all control schools are offered participation in the following year. The flow of the trial is shown in the CONSORT diagram in Fig. 1.

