### Randomisation procedure

Groups of recruited schools will be randomised in blocks of even numbers. Recruiting schools is an on-going process and the smallest block size will be two, such that once a pair of schools is recruited, and if others are unlikely to be recruited soon, the pair will be randomised. Where possible, the block size will be larger. Once at least two schools have been recruited and the Head Teachers’ letters returned, the schools are numbered and documented and dated. The randomisation is then conducted off-site by a statistician at the MRC Lifecourse Epidemiology Unit using computer-generated sequences, with no knowledge of the schools in question. Prior to randomisation, no matching of schools takes place. Schools require the information about their status in a timely fashion in order to plan their curriculum/allocate staff and resources in advance. Schools are recruited throughout the year, and it would be difficult to match schools by exact criteria. We are recruiting from a large area and a major consideration when calculating the numbers of schools necessary to recruit was to ensure a wide representation of schools/pupils.

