### Power calculations

Using data on behaviour (z-scores), validated in our previous research in young adults in and around Southampton [43], we have estimated an intra-class correlation of 0.035, but to be conservative we have rounded this up to 0.04. We propose to sample three Year 9 (aged 13 to 14 years) classes from each school, averaging 90 students from each school. Using 90 as our cluster size we estimate that with 14 clusters in each group, we will have 80 % power at the 5 % level of significance to detect a difference in change in our primary outcome score of 0.25 SDs from the beginning to end of the school year between the intervention and control schools. Comparable effect sizes have been considered in other health interventions as being meaningful in terms of the impact on health behaviours, and our level of 0.25 SDs falls in the mid-range of effect sizes reported in a meta-synthesis of meta-analyses of behaviour change interventions in the general population [47]. As described above, we will study 32 year groups, thus allowing some leeway for dropouts. To minimise loss of pupils to follow-up, we will request class lists for each participating class (both from the intervention and control schools), so that missing participants at each stage of the follow-up can be identified and asked to complete the questionnaires.

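### The stated model names no school-year term although allocation is planned 8 to 8 in each of two years, and it attaches no small-sample method to analyses of 28 to 32 schools

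*Protocol article*

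**What the plan says.** **Allocation.** Under Trial design, 16 schools are to be recruited in 2014–15; of these, "eight will therefore be intervention schools and their Year 9 students will take part in the LifeLab programme", and the other eight are controls. The same is planned for 2015–16. Under Randomisation procedure, "Groups of recruited schools will be randomised in blocks of even numbers", with pairs as the smallest block and no prior matching. School year is not declared as a stratum.

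**Model.** Under Statistical analyses, random-effects models handle the clustering: multi-level linear regression for continuous measures, which covers the primary literacy score, and multi-level logistic or Poisson regression for binary ones ("Poisson regression models with robust variance (for more common outcomes) will be used for binary outcome variables"). The endpoint is the 12-month result adjusted for baseline responses. No term for school year or block is named.

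**Few clusters.** The same section states: "The number of clusters is relatively small, and summary analyses will be conducted at school level", and gives feedback to schools as one reason. It names no reference distribution, degrees-of-freedom method or correction to the robust variance. It does not say whether the school-level summaries are inferential.

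**Size.** Power calculations takes 90 pupils per school and 14 schools per arm as sufficient for its target: "we will have 80 % power at the 5 % level of significance to detect a difference in change in our primary outcome score of 0.25 SDs". In all, 32 schools are planned, to allow for dropout.

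**The concern.** If each year contributes equal numbers of schools to both arms, a difference between the years cannot bias the arm comparison. It still inflates the residual variation between schools unless the model contains the year. The standard error is then too large, the test rejects less often than 5% under the null, and power is lost. The two years could differ: the intervention section says that the teaching materials are still being developed.

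The second issue works the other way. With about 30 schools, a random-effects or robust-variance estimate referred to the normal distribution rejects too often, because the between-school variance rests on about 30 degrees of freedom. The article recognises that clusters are few, but answers with school-level summaries rather than a correction to the pupil-level models. One outcome may then carry two p-values with no statement of which decides.

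**Working it through.** **Inputs from Power calculations.** Effect 0.25 SD, so SD = 1; ICC 0.04 ("we have estimated an intra-class correlation of 0.035, but to be conservative we have rounded this up to 0.04"); 90 pupils per school; 14 schools per arm needed, 16 planned. A two-sided 5% test is assumed, since the article does not state sidedness.

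**1. The plan's own figure.** Design effect = 1 + 89 × 0.04 = 4.56. Individual randomisation needs 252 per arm, so 252 × 4.56 / 90 = 12.77, or 13 schools per arm by the normal formula. A noncentral t on 2k − 2 degrees of freedom gives 77.5% power at k = 13 and 80.7% at k = 14. The stated 14 per arm is therefore reproduced when a small-cluster allowance is made.

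**2. Cost of leaving out school year.** The variance of a school mean is v = 0.04 + 0.96/90 = 0.0507. With 16 schools per arm, SE = √(2 × 0.0507/16) = 0.0796 and 0.25/0.0796 = 3.14.

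Let δ be the cohort difference left after baseline adjustment, with each year balanced by arm. The true SE does not change, but the expected residual variance in a model without year becomes v + Kδ²/[4(K − 2)] for K schools. At K = 32 and δ = 0.2 this is 0.0507 + 0.0107 = 0.0613, so the estimated SE is too large by a factor of about √(0.0613/0.0507) = 1.10.

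Simulated power of the t-test on school means (K − 2 degrees of freedom without year, K − 3 with it) is:

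| Residual shift δ (assumed) | 32 schools, without / with year | 28 schools, without / with year |
|---|---|---|
| 0 | 86% / 86% | 81% / 81% |
| 0.1 SD | 85% / 86% | 79% / 81% |
| 0.2 SD | 81% / 86% | 75% / 81% |
| 0.3 SD | 74% / 86% | 67% / 81% |

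At δ = 0 the noncentral t gives 86.0% against 85.9% at 32 schools and 80.7% against 80.6% at 28, so the unneeded term costs about 0.1 point. Without the term, the actual size of the 5% t-test is about 4.4% at 0.1 SD, 3.1% to 3.2% at 0.2 SD and 1.8% to 1.9% at 0.3 SD. With it, size returns to about 5.0%.

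**3. Size if a normal reference were used, with no cohort shift.** For the linear model the size is P(|t| > 1.96) on K − 2 degrees of freedom with a REML-type variance. With a maximum-likelihood variance the cut-off is multiplied by √[(K − 2)/K].

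- 28 schools: 6.1% (REML-type), 7.0% (maximum likelihood).
- 32 schools: 5.9% (REML-type), 6.7% (maximum likelihood).
- Robust Poisson (assumed prevalence 20% to 40%, ICC 0.04, simulated): 6.4% to 6.7% at 28 schools, 6.3% to 6.6% at 32.
- With a t on K − 2: school-level t-test 4.9% to 5.1%; robust Poisson 5.3% to 5.6%. For Poisson, the t reference removes most but not all of the excess.

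**4. The two effects together.** A REML-type variance, a normal reference and year omitted give 5.3% to 5.5% at a shift of 0.1 SD and 3.8% to 4.0% at 0.2 SD. The conservatism hides the inflation. If year is added while the normal reference is kept, the linear size with no shift is 6.2% (REML-type) or 7.6% (maximum likelihood) at 28 schools. The two changes therefore belong together.

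**The case against.** The strongest reply is that a condensed article need not give a full covariate list or a degrees-of-freedom method; both are commonly left to an analysis plan, which is not shown here. That stands, and it limits the small-sample point to a conditional one.

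A reader might infer that the model adjusts for baseline and nothing else, that large-sample tests are planned, and that the p-values are therefore miscalibrated. The article does not support this:

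- It does not exclude further covariates and states no reference distribution. The 14 schools per arm fit a t-based calculation better than a normal one.
- Robust variance is named for common binary outcomes. The primary score falls under multi-level linear regression, so the robust-variance issue does not reach the primary p-value.
- The section acknowledges few clusters and adds school-level summaries. A school-level t-test holds about 5%, although the text does not make it the deciding analysis.
- The two effects push test size in opposite directions, so the net error depends on an unknown cohort effect.

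The cohort point also has limits. Sixteen schools per year is an aim, and balance within a year requires that blocks do not straddle years. A difference already visible at baseline may be absorbed by the planned adjustment. The shifts used here are assumptions; 0.3 SD exceeds the target effect itself. At 0.1 SD the loss is only 1 to 2 points, and at 0.2 SD with all 32 schools power is still above the planned 80%.

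What remains is that the article does describe a model. A one-term addition matching the planned allocation improves it at almost no cost, and the article raises the few-clusters problem without saying how the named models will deal with it.

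**Conclusion.** The point holds as a modest improvement to the stated analysis. Leaving out school year does not bias the effect estimate when the arms are balanced within year. It makes the test conservative and costs about 1, 5 or 12 points of power at 32 schools for residual shifts of 0.1, 0.2 or 0.3 SD. At 28 schools, the number on which the power claim rests, shifts of 0.2 and 0.3 SD bring power to 75% and 67%, and even 0.1 SD takes it just under 80%.

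Separately, and only if normal-based tests were used, type I error would be about 5.9% to 7.0% for the linear model and 6.3% to 6.7% for robust Poisson on binary outcomes.

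These figures assume ICC 0.04, 90 pupils in every school for the linear model, equal numbers per arm in each year, and the cohort shifts and prevalences stated above, none of which the article gives. They do not show that the trial's p-values will be wrong.

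**What to change.** - Make one primary analysis: a multi-level linear model for the 12-month score with arm, baseline score and school-year cohort as fixed effects and school as a random effect, fitted by REML with Satterthwaite or Kenward-Roger degrees of freedom.
- For Poisson models, use a robust variance corrected for few clusters, with a t reference on schools minus parameters.
- Label the school-level summaries as supportive, so that one analysis decides.
- Do not fit every randomisation block: 32 schools in pairs make 16 blocks and would use up to 15 degrees of freedom.

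The cost is a change of wording, one degree of freedom for school year, and intervals slightly wider than uncorrected ones. No further data are needed. The change is best fixed before follow-up outcomes are seen.

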### Financial evaluation

These data will be combined with appropriate unit cost data to estimate the costs of LifeLab. We will use the health and nutrition literacy score as the outcome measure in a cost-effectiveness analysis and will estimate the cost per unit change in this score. These data will be important in determining the level of support needed to sustain LifeLab on a longer term basis.

### Power calculations

Using data on behaviour (z-scores), validated in our previous research in young adults in and around Southampton [43], we have estimated an intra-class correlation of 0.035, but to be conservative we have rounded this up to 0.04. We propose to sample three Year 9 (aged 13 to 14 years) classes from each school, averaging 90 students from each school. Using 90 as our cluster size we estimate that with 14 clusters in each group, we will have 80 % power at the 5 % level of significance to detect a difference in change in our primary outcome score of 0.25 SDs from the beginning to end of the school year between the intervention and control schools. Comparable effect sizes have been considered in other health interventions as being meaningful in terms of the impact on health behaviours, and our level of 0.25 SDs falls in the mid-range of effect sizes reported in a meta-synthesis of meta-analyses of behaviour change interventions in the general population [47]. As described above, we will study 32 year groups, thus allowing some leeway for dropouts. To minimise loss of pupils to follow-up, we will request class lists for each participating class (both from the intervention and control schools), so that missing participants at each stage of the follow-up can be identified and asked to complete the questionnaires.

## Discussion

A formal assessment of LifeLab would show the value of the programme in educating teenagers about their cardiovascular health and about the value of science. It would point to ways to improve and develop the LifeLab concept and identify the activities that have the most profound effect on the students. If shown to be successful, this would provide the impetus to sustain LifeLab in Southampton and encourage the development of similar initiatives in other cities in the UK and around the world. There are a few projects similar to LifeLab which have been established in other cities worldwide. The Liggins Institute was at the forefront of this work with LENScience [48], and Lord Winston established the Reach Out Lab at Imperial College, which, although a similar concept offering school students opportunities to experience science outside of the school environment, has different aims, focusing on motivating high attaining children to consider careers in science-related subjects. Plans are now being developed for laboratories elsewhere, similar to LifeLab, including in other countries such as Australia, South Africa and Ireland.

Improving the diets and lifestyles of young people is an important route both to reducing NCDs in their later lives but also improving the health of the next generation. By targeting children from all backgrounds this provides a form of societal intervention, such as has recently been advocated as likely to have a greater impact on cardiovascular disease inequalities than targeting those at high risk of the disease [49].

## Trial status

Recruitment for the RCT has been initiated, and 18 schools have been recruited and have already progressed through the randomisation phase.

## Abbreviations

NCD: non-communicable disease
RCT: randomised control trial
CPR: cardio-pulmonary resuscitation
SWS: Southampton Women’s Survey
